### Recruitment

Participants will be recruited from community-based HIV counselling and testing platforms established in study communities for the purpose of this study. Consent and enrolment will be conducted by field-based enrolment counsellors.

#### HIV testing and testing platforms

Two different CBCT modalities, *pop-up site* and *home-based testing*, will be leveraged in each community. HIV testing will be conducted in accordance with South African national guidelines [50]. Referrals to local HIV treatment services will be provided to those with a confirmed positive result.

##### Pop-up testing sites

Three pop-up testing sites will be leveraged in each study community. The main site (Site A) will be a fixed-positioned testing venue co-located with a centralized community venue for the full duration of the study. A second site (Site B) will be a semi-mobile container co-located with another recognizable community venue during enrolment. A third site (Site C) will be a highly mobile testing tent placed at peripheral locations in each community, and repositioned 2–3 times during enrolment.

##### Door-to-door home-based testing

Prior to initiating home-based testing activities, GIS maps will be obtained for each community, with 24 urban and 26 rural small-block areas delineated and individual houses plotted for targeted testing. Detailed maps and electronic tablets will be used to track the small-block areas and houses visited and tested. Home-based testing will be performed until all houses are visited at least once.

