### Study location

This study is being conducted in Buffalo City Metro (BCM) Health District, Eastern Cape Province, South Africa (Fig. 1). In 2016, BCM had an estimated mid-year population of 834,998 people. In 2016, the South African National Department of Health estimated that BCM had a general population HIV prevalence of 12.4% and incidence of 0.54%; an adult (15+ years old) HIV prevalence of 17.1% and incidence of 0.74%; and a female youth (age 15–24 years) HIV prevalence of 12.8% and incidence of 2.40% [41]. Within BCM, our study will be conducted in one urban and one rural community. Selection of study communities was conducted in consultation with the BCM Department of health and was informed by census data, absence of other ongoing HIV prevention studies, and community willingness to be involved in the study.

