### Primary and secondary outcomes

For Aim 1, our primary outcome will be the proportion of eligible individuals accepting PrEP as part of CBCT services. Secondary outcomes will include (1) stratification of PrEP initiation by both location and CBCT platform; (2) in-depth qualitative understanding of PrEP initiation; (3) correlates of immediate, delayed, and no PrEP initiation; and (4) comparison of sexual behaviours, risk profiles, and self-perception of risk in immediate, delayed, and never acceptors. Using the IMB model to inform the selection of variables and contextualization of results, an assessment of determinants of PrEP uptake will include (1) socio-demographic factors, (2) risk behaviours, (3) self-perception of risk, (4) previous knowledge of PrEP and perception of those taking PrEP, (5) partner characteristics and HIV status, (6) HIV-related stigma, and (7) screening scores for depression, substance abuse, and social support. Baseline STIs will be used as an independent marker of sexual risk behaviour, and to validate self-reported sexual risk behaviours and self-perception of risk.

For Aim 2, the primary outcome will be a comparison of TFV-DP levels by study arm at months 3, 6, 12, 18, and 24, with a 12-month primary outcome and 24-month assessment of intervention durability. Based on cumulative adherence behaviour, as measured in iPrEX OLE [14], adherence will be categorized as (1) *low adherence* (≤ 3 tablets per week; ≤ 699 fmol/DBS punch), and (2) *high adherence* (4–7 tablets per week; ≥ 700 fmol/DBS punch). Analysis of primary outcomes will be conducted on an intention-to-treat basis. Secondary outcomes will include (1) predictors of PrEP adherence after adjusting for study arm, socio-demographic factors, exposure to adherence support activities, and risk profiles; (2) characterization of changes in sexual behaviours and risk profiles following PrEP initiation; (3) proportion of individuals who discontinue PrEP and factors associated with discontinuation; (4) proportion of individuals who discontinue but subsequently restart PrEP and characteristics associated with this subgroup; (5) factors associated with of patterns of PrEP use; and (6) profiles of individuals that may benefit more from group-based vs. individualized adherence support.

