### Data analysis

Descriptive statistics (e.g. means, standard deviations/variances, medians with inter-quartile ranges, and frequency distributions) will be used to describe participant demographic characteristics. The chi-squared statistic test will be used for categorical variables whereas T-test (parametric) or Wilcoxon rank sum test (non-parametric) will be applied for continuous variables. Transformations of outcome variables will be explored and performed if appropriate. Multivariate logistic regression models will be performed to examine associations between covariates. Since data is collected on one subject over time, the data will be treated as longitudinal data. Generalized linear mixed effect models will be fitted to determine associations of interest with time and intervention effects included as fixed effects and allowing for subject-specific random effects. Alternatively, generalized estimating equations can be used to account for any correlations of repeated data measures, when assessing determinants of PrEP adherence at time points provided we have balanced data with ignorable missing patterns. Time-to-event analysis will be conducted using Kaplan-Meier plots. To determine possible associations with covariates, a Cox-proportional hazard will be used. If the proportional hazard assumption does not hold, an accelerated failure time model will be used. Missing data due to loss to follow-up is inadvertent and inevitable. The extent of missing data will be assessed in the primary analysis. The primary analysis will be conducted under the assumption of data Missing at Random (MAR). As such, longitudinal likelihood-based data analysis, utilizing all the observed pre-deviation data from each participant will be employed. Thereafter, multiple imputation (MI) method will be employed under the primary MAR assumption, and Rubin’s rule will be followed to combine results. Sensitivity to deviation from the MAR assumption will be investigated. Intention to treat (ITT) assessment with complete case approaches where necessary will be implemented in cases of non-adherence to randomization assignment. Depending on the extent of non-adherence, the “as treated (AT)” approaches may be employed to analyse participants according to the intervention received regardless to their randomized allocation. A marker of level of adherence can also be included in the models. Patterns of PrEP use will be identified using latent class models or clustering techniques and the association of factors with these latent classes will be examined using multinomial logistic regression modelling. For all statistical investigations, tests for significance will be two-tailed. Analyses will be conducted using STATA 13.0 or R version 4.

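### Aim 1 tests treat women as independent although they are recruited by house, small-block area and pop-up position; the comparison of testing platforms is the result most exposed

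*Protocol article*

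**What the plan says.** - **Home-based recruitment** (Door-to-door home-based testing): each community is mapped, with "24 urban and 26 rural small-block areas delineated and individual houses plotted for targeted testing". Coverage is meant to be complete: "Home-based testing will be performed until all houses are visited at least once". On recording: "Detailed maps and electronic tablets will be used to track the small-block areas and houses visited and tested".
- **Pop-up recruitment** (Pop-up testing sites): "Three pop-up testing sites will be leveraged in each study community". Site A is fixed, Site B is a semi-mobile container, and Site C is a tent "repositioned 2–3 times during enrolment".
- **Setting** (Study location): "our study will be conducted in one urban and one rural community".
- **Aim 1 outcomes** (Primary and secondary outcomes): "our primary outcome will be the proportion of eligible individuals accepting PrEP as part of CBCT services". Secondary outcomes include initiation by location and by testing platform, and the correlates of immediate, delayed and no initiation.
- **Analysis** (Data analysis): a chi-squared test for categorical variables, and "Multivariate logistic regression models will be performed to examine associations between covariates". Random effects per subject, or alternatively generalized estimating equations, are named for repeated measurements over time. No term or variance method is named for house, block or pop-up position.

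**The concern.** Aim 1 is cross-sectional, so the provisions for repeated measures do not reach it. What remains is a chi-squared test and logistic regression, both of which assume that one woman's outcome tells nothing about the next woman's.

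The recruitment makes that assumption doubtful. The eligibility list sets no limit of one woman per house, so relatives may both enter. The PrEP study sites are placed with pop-up sites A and B (Referral for PrEP services and study enrolment). A woman tested there can start where she was tested, while one tested at home or at Site C has to travel. Travel is much the same for everyone in a block or at a tent position, and it bears directly on whether initiation is immediate, delayed or absent.

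The platform comparison is the most exposed. Platform is constant within every block and every position, so the design effect applies in full, and the pop-up side rests on few positions. If the naive standard error is too small, a difference between platforms could be declared too readily, and the article intends its results to inform how PrEP services are scaled up.

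**Working it through.** **The plan's own figure.** The only sample size in the article is for Aim 2: a chi-squared test with 2 degrees of freedom, alpha 0.05, 80% power and effect size 0.15 (read as Cohen's w). The required noncentrality is 9.635, so N = 9.635 / 0.15² = 428.2, rounded up to 429. With 10% attrition, 429 / 0.9 = 476.7, rounded up to 477, against 480 stated. It reproduces. It concerns individually randomized women and is not touched by this point. No sample size or precision target is given for Aim 1.

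**Number of clusters, from the document.**
- Home-based: 24 + 26 = 50 small-block areas.
- Pop-up: Site C moved 2 to 3 times gives 3 to 4 positions. With A and B that is 5 to 6 per community, or 10 to 12 over two communities.

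**Assumed, because the documents are silent.** 500 women tested on each platform, evenly spread over 50 blocks (m = 10 each) and 10 positions (m = 50 each), with the same ICC on both platforms, from 0 to 0.05.

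**Formulas.**
- Design effect: DE = 1 + (m − 1) × ICC.
- Platform contrast with equal numbers: standard-error ratio r = √[(DE_home + DE_pop-up) / 2].
- True two-sided error of a nominal 5% test: 2 × [1 − Φ(1.96 / r)].
- Naive 95% half-width at p = 0.5: 1.96 × √(0.5 / 500) = 6.2 percentage points.

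| ICC | DE home | DE pop-up | r | True error | Half-width (points) |
|---|---|---|---|---|---|
| 0 | 1.00 | 1.00 | 1.00 | 5% | 6.2 |
| 0.01 | 1.09 | 1.49 | 1.14 | 8% | 7.0 |
| 0.02 | 1.18 | 1.98 | 1.26 | 12% | 7.8 |
| 0.05 | 1.45 | 3.45 | 1.57 | 21% | 9.7 |

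**Sensitivity to the assumptions, at ICC 0.05.**
- 12 positions instead of 10: m = 500 / 12 = 41.7, DE = 3.03, r = √[(1.45 + 3.03) / 2] = 1.50, true error about 19%.
- 1,000 women per platform (m = 20 and 100): DE = 1.95 and 5.95, r = 1.99, true error 32%.

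**An interval for home-based acceptance, if one is reported.** With 500 women and p = 0.5, the naive half-width is 1.96 × √(0.25 / 500) = 4.4 points. It becomes 4.6, 4.8 and 5.3 points at ICC 0.01, 0.02 and 0.05.

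**The case against.** Four arguments weigh against the point.

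1. **The blocks are not a cluster sample.** Every house is to be visited, and the blocks are described as a way of tracking fieldwork. This stands: for home-based acceptance in these two communities there is no first-stage sampling variance. It does not remove correlation between women in the same house or block. Nor does it cover pop-up attenders, who are not a census, or inference beyond these communities, which the Discussion has in view.
2. **No stated error bar is wrong.** A reader might infer that the intervals for the Aim 1 primary proportion are too narrow. The article states no interval, test or precision for it, so there the point is only prospective.
3. **Most listed correlates differ between women.** Socio-demographic factors, risk behaviour, perceived risk, knowledge, partner characteristics, stigma and screening scores are collected from each woman. A reader might apply the full design effect to all of them, but that overstates the problem. Of the named results, platform is the one within each community that takes the full effect.
4. **The article is condensed, and the size is assumed.** Both are true. With an ICC of 0 nothing changes, and the full protocol may say more. But the article does state both the tests and the correlation structure, and the structure it states is not the one that Aim 1 recruitment creates.

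**Conclusion.** The point holds in a limited form. As written, the Aim 1 comparisons treat women as independent although they come from shared houses, 50 blocks and about 10 to 12 pop-up positions. If outcomes are correlated within these units, standard errors are likely too small, chiefly for pop-up versus home-based testing. The 5% to 21% range for the true error of a nominal 5% test rests on 500 women per platform, 10 positions, even cluster sizes and an ICC from 0 to 0.05. None of the women, cluster-size or ICC values is given in the documents, so the range illustrates the risk and does not estimate it. The documents do not support saying that Aim 1 intervals are too narrow as a fact. The change is worth making because it is cheap, but it does not put the trial's main comparison in doubt: Aim 2 and its 480 participants are unaffected.

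**What to change.** For the platform contrast, for any area-level correlate, and for any interval reported for Aim 1 acceptance, use cluster-robust standard errors. The cluster is the small-block area for home-based women and the site position for pop-up women.

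- Keep community as a fixed effect in the models.
- Apply a small-sample correction, because there are only about 10 to 12 pop-up positions.
- Do not rely on a block random intercept alone: it assumes independence within a block once the block effect is given, so extra correlation between women in one house would remain. Robust variance at block level covers this, because houses lie within blocks.
- Link the block or position identifier to each woman's record. Blocks and houses are tracked on tablets, but the article does not say that they are tied to individual questionnaires, and it does not mention recording the tent position.

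The cost is a sentence or two in the analysis plan, a standard software option and the linkage. The downside is somewhat wider intervals; if the correlation is near zero, little is lost.

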#### PrEP initiation and study enrolment

##### Baseline screening for referral for PrEP study and services

Prior to screening, participants will be asked to provide fingerprints to facilitate participant identification during subsequent study activities; fingerprints will be collected using the FS88 Futronic Fingerprint Scanner [Futronic Technology Company, Kwai Fong, Hong Kong]. Participants will then be asked to complete an audio computer-assisted self-interviewing (ACASI) questionnaire collecting socio-demographic, behavioural, and clinical histories; HIV knowledge, attitudes, and practice; and a self-reported HIV risk survey. Upon completing the ACASI, participants will watch a PrEP informational video [51], followed by an interviewer-administered screening tool to assess whether the participant is currently (1) interested in learning more about PrEP, (2) interested in taking PrEP, (3) using post-exposure prophylaxis (PEP), (4) participating in other HIV prevention studies, (5) pregnant, (6) breast feeding, (7) on TB treatment, or (8) has signs or symptoms of acute HIV infection. Responses will be captured in real time using REDCap.

##### Inclusion/exclusion criteria

A candidate is eligible for referral to PrEP initiation services if they (1) are aged 16–25 years; (2) self-identify as female; (3) have a HIV-negative test result obtained from a study-associated CBCT site; (4) plan on residing in the study community for at least 12 months; (5) complete the baseline questionnaire; (6) express interest in taking PrEP; (7) not taking TB treatment; (8) not pregnant or breastfeeding; (9) not currently using PEP; (10) not currently participating in other HIV prevention studies; (11) do not have signs or symptoms of acute HIV infection; (12) understand English or IsiXhosa. Of note, given the likelihood of social desirability bias, structural risk factors, and the dynamic nature of HIV risk among South African AGYW, prior sexual activity will not be used as inclusion/exclusion criterion [8, 52, 53].

##### Referral for PrEP services and study enrolment

Eligible participants interested in PrEP will be provided a copy of their HIV test results and a referral letter for PrEP initiation at our study sites, which will be co-located with pop-up testing sites A and B. Upon presenting to a PrEP study site, participants will be consented, asked to provide contact details, tested for syphilis and pregnancy, and asked to submit a self-collected vaginal swab for further STI testing (Table 2). If pregnant, participants will be provided a referral letter for antenatal care services in lieu of PrEP initiation, as South Africa has not yet approved PrEP initiation during pregnancy. Prior to departure, participants will receive their syphilis test results, with a treatment referral if applicable.

Participants will be asked to provide a blood sample for hepatitis B testing and creatinine clearance, randomized, and then provided a 30-day supply (1 bottle) of DIDIVIR (CIPLA generic for Emtricitabine 200 mg/ Tenofovir Disoproxil Fumarate 300 mg); those randomized to an intervention group will be reminded of their first adherence session date. All participants will be asked to return for an orientation visit 2 weeks post-enrolment to meet with their adherence counsellor, and a study nurse to review any test results, assess side effects and acute HIV symptoms, and receive the first of three hepatitis B injections if indicated.

### Data collection, management, and oversight

A mixed-methods approach will be used to collect data from participants and study staff throughout the 2-year study follow-up period.

#### Quantitative data

*Quantitative data* will be captured at baseline and again at months 3, 12, and 24 via ACASI, about participants’ sexual behaviour, risk factors, self-perception of HIV acquisition risk, partner characteristics and HIV status, knowledge and attitudes towards PrEP, perceived barriers and facilitators of PrEP uptake and adherence, projected HIV stigma, alcohol and drug use, mental health, and social support [54–57]. Basic adherence tracking, specimen collection, test results, and participant timelines will be monitored on REDCap.

#### Qualitative data

*Qualitative data* (Table 4) will be collected using in-depth interviews (IDIs) and community mapping exercises (CMEs) with AGYW, focus group discussions (FGDs) with community advisory board members, and staff exchange programmes. All IDI and FGD guides will be semi-structured, and studies will be conducted in the preferred language of the participant.

**Table 4 Tab4:** Qualitative data collection schedule

Category	Case definition	Data collection method	Participant type	# of interviews
**Special circumstances among study participants**				
Seroconverts	Participant tests HIV positive during any follow visit. HIV test confirmed with ELISA test.	IDI	PrEP Participant	3 IDIs
Discontinued PrEP	Participants who decide to discontinue PrEP during any time of the study follow-up period.	IDI	PrEP Participant	9 IDIs (3 per arm)
Two or more consecutive missed visits	Participants who missed two or more consecutive adherence visits during follow-up period.	IDI	PrEP Participant	12 IDIs
Reported social harms	Participants who report any type of social harm due to study participation. i.e. participants treated unfairly and experiencing problems being accepted by their families, partners, and/or communities due to participation in the study	IDI	PrEP Participant	All Cases of Social Harms
Unique pattern of medication use	Participants who have a unique pattern of medication use as identified by adherence counsellors or study nurses. i.e. Use over holidays and/or over weekends only	IDI	PrEP Participant	9 IDIs (3 per arm)
Never presented for medication refill following enrollment	Participants who never presented to study sites for adherence sessions/medication collection after initiating PrEP.	IDI	PrEP Participant	15 IDIs
**PrEP uptake from community platforms**				
Immediate acceptors	Participants who consent to study and receive supply of PrEP the day of screening and study introduction.	IDI	Pop-up Site Testing Enrolment	15 IDIs
Immediate presenters	Participants who present to study sites for PrEP initiation within 0-3 days of completing baseline questionnaire.	IDI	Home-based Testing Enrolment	15 IDIs
Early presenters	Participants who present to study sites for PrEP initiation within 4-14 days of completing baseline questionnaire.	IDI	Home-based Testing Enrolment	15 IDIs
Late presenters	Participants who present to study sites for PrEP initiation within 15-30 days of completing baseline questionnaire.	IDI	Home-based Testing Enrolment	15 IDIs
Never presenters	Participants who never presented to study sites after completing baseline questionnaire.	IDI	Home-based Testing Enrolment	15 IDIs
**Experiences with taking PrEP and engaging in adherence support activities**				
High adherence	Active participants who have attended more than one adherence session with DBS levels ≥ 700 fmol/punch.	IDI and CME	PrEP Participants	20 IDIs (5 per intervention arm per site)
Low adherence	Active participants who have attended more than one adherence session with DBS levels ≤ 699 fmol/punch.	IDI and CME	PrEP Participants	20 IDIs (5 per intervention arm per site)
**Process evaluation and staff implementation experiences**				
PrEP field staff	Interviews with field staff, including research nurses, adherence counsellors, and field workers to understand their experiences with PrEP implementation at a community-based level.	IDI	Field Staff	12 IDIs (6 per site)
Observational exchange exercise	Exchange of one staff member per site to observe differences in staff interaction with PrEP participants that may influence participant adherence and attendance.	Staff Exchange	Field Staff	1 day per site
**Community preparation and engagement**				
CAB members	Active community advisory members who advised study staff on study implementation, study progress, and community engagement.	FGD	CAB Members	4 FGDs (2 per site)

#### AGYW interviews

*AGYW interviews* will be used to understand their decisions on whether or not to access PrEP services, timing of PrEP initiation, early product experience, and disclosure challenges. A second cadre of interviews will focus on motivation of continued PrEP use and factors influencing adherence. During these interviews, participants will complete two mapping activities: (1) community map of their neighbourhoods to outline social settings influencing PrEP uptake and adherence; and (2) map of their home to describe resources (water/ food security, privacy etc.) and family factors influencing PrEP management and dosing plans. A third group of interviews will explore special circumstances occurring among study participants.

